#### Participant Assessment

Before the first coaching session, the participant will fill out the diabetes distress scale (DDS) [18] and a subset of the Summary of Diabetes Self-Care Activities questionnaire [30] focused on medication-taking, dietary, and physical activity behaviors. Only patients with significant DD (DDS score ≥2.0) will be included in this study. The health coach will review the DDS report to obtain information on the specific type of distress (eg, regimen distress) and the primary sources of distress, that is, the specific things about diabetes management that are upsetting to that particular person (eg, not feeling motivated to keep up with diabetes self-management; see Table 1).

#### First Coaching Session

At the first coaching session, building on the findings from the participant assessment, the coach will probe further to identify possible targets for the coaching intervention (Table 1). The targets define the specific goals related to DD or the underlying stressors that the participant would like to resolve or achieve at the end of the intervention. As necessary, the coach might also explore participant’s priorities, confidence, and readiness to change concerning different aspects of diabetes self-management. The coach then explores the participant’s willingness to embark on the coaching journey, discusses the findings from the assessment, and works with the participant to identify possible coaching targets (Table 1). The participant prioritizes the coaching targets and creates goals that he or she will like to achieve and a 3-month action plan.

#### Subsequent Coaching Sessions

Participants’ progress will be reviewed at subsequent coaching sessions. Most coaching sessions focus on a specific topic, helping clients navigate and overcome emerging challenges on their change journey [9]. As necessary, the coach will tap into her or his coaching toolbox to help elevate the participant’s energy, brainstorm strategies for problem solving, develop solutions, meet challenges, and set and agree on subsequent goals [9].

For purposes of quality control, the health coach will take notes on client interactions and coaching techniques used for review with the investigators. This allows ongoing feedback to ensure appropriateness of the intervention.

### Training of Intervention Staff

HC will be provided by a registered dietitian trained and certified as a Health and Wellness Coach by one of the “Transition Programs” approved by the International Consortium for Health and Wellness Coaching [31]. The International Consortium for Health and Wellness Coaching is an organization working to standardize HC practice in the United States and across the world. DD-specific education (Multimedia Appendix 1) for participants in both arms of the study will be provided by designated medical assistants in the clinic who were trained to provide this education in a consistent manner (Textbox 1).

### Study Population, Inclusion, and Exclusion Criteria

The target population is adult patients with diabetes and DD at the study clinic. Textbox 2 summarizes the inclusion and exclusion criteria.

**Table 1 table1:** Identifying the focus of the coaching intervention from the type and sources of diabetes distress using the diabetes distress scale.

DDS^a^ subscale	Questions (from DDS)	Possible coaching targets
Regimen distress	Not feeling confident in my day-to-day ability to manage diabetes; Feeling that I am not testing my blood sugars frequently enough; Feeling that I am often failing with my diabetes routine; Feeling that I am not sticking closely enough to a good meal plan; Not feeling motivated to keep up my diabetes self-management	Perception of low self-efficacy for diabetes self-care; Perception of low motivation for diabetes self-care; Perception of lack of success in following diabetes self-care plan
Emotional burden	Feeling that diabetes is taking up too much of my mental and physical energy every day; Feeling angry, scared, depressed, or a mixture of these feelings when I think about living with diabetes; Feeling that I will end up with serious long-term complications, no matter what I do; Feeling that diabetes controls my life; Feeling overwhelmed by the demands of living with diabetes	Low level of perceived ability to influence outcomes; Low level of perceived ability to manage emotions
Interpersonal distress	Feeling that friends or family are not supportive enough of self-care efforts; Feeling that friends or family do not appreciate how difficult living with diabetes can be; Feeling that friends or family do not give me the emotional support that I would like	Perception of low levels of social support for dealing with diabetes
Physician-related distress	Feeling that my doctor does not know enough about diabetes and diabetes care; Feeling that my doctor does not give me clear enough directions on how to manage my diabetes; Feeling that my doctor does not take my concerns seriously enough; Feeling that I do not have a doctor who I can see regularly enough about my diabetes	Perception of dissatisfaction with the quality of patient-provider communication; Perception of the need to seek a better or regular provider

^a^DDS: diabetes distress scale.

Inclusion and exclusion criteria for the Coaching and Education for Diabetes Distress trial.Inclusion criteriaHas had a diagnosis of type 2 diabetes for at least 6 monthsAged 18 to 75 yearsMost recent hemoglobin A_1c_ taken within 30 days was 8.0 or aboveAt least a moderate diabetes distress, operationalized as a mean score of 2.0 or more on the 17-item diabetes distress scale [32]Exclusion criteriaModerately-severe to severe depression: Patient health questionnaire-9 score 15 or above [17]Other severe mental health disorder (eg, Alzheimer’s or schizophrenia)Current pregnancySevere diabetes complications or functional deficits (eg, kidney failure requiring dialysis, amputation, or blindness)

### Study Arm Assignment

Figure 1 outlines the screening, recruitment, and randomization process for the study. A random sorting randomization algorithm will be implemented using PASS software version 15.0.3 (NCSS LLC, Kaysville, UT) to generate a randomization list that will dictate assignment of patients into either the intervention or control (usual care) arm. To ensure the algorithm results in the desired group sample sizes, the program search is conducted by creating a randomization list using the user-specified randomization algorithm and then looking at the final sample sizes. If the sample sizes do not match the target sample sizes for all groups, then the list is discarded and the algorithm is restarted. This process continues until a list with the exact sample sizes is found.

**Figure 1 figure1:**
[figure not shown]
Screening, recruitment, and randomization process for Coaching and Education for Diabetes Distress trial.

### Sample Size Determination

The study requires a total sample of 156 participants, 39 in the intervention arm and 117 in the control arm. Calculations were based on the following assumptions: a power of 80%, alpha (type I error rate) of 5%, an effect size (difference in mean change in DD between the 2 groups) of 0.5, which is considered both clinically significant and at least of moderate magnitude [7], a DD SD of 0.89 and 0.81, respectively, at baseline and at follow-up [15], a correlation (ρ) of 0.5 between a pair of observations made longitudinally on the same subject, and accounting for a possible attrition rate of 20%. It has been shown that when research costs vary among treatments, it is economically efficient to randomize more participants to the cheaper arm without compromising validity [33]. Therefore, to achieve adequate statistical power within fiscal constraints, more participants will be recruited in the control arm than in the intervention arm (at a ratio of 3:1). On the basis of these assumptions and the stated sample size, this study achieves 80% statistical power to detect differences in the mean change in DD of 0.5 between the 2 groups, but it has more than 90% power to detect differences in mean changes in DD of 0.6 or higher (Figure 2).

### Measures and Data Collection

The variables that will be measured and the timeframe for data collection are summarized in Table 2. The primary outcome measure will be short-term (6 months) changes in DD score. Secondary outcome measures of interest are willingness-to-pay (WTP) for and satisfaction with HC, as well as changes in HbA_1c_ and diabetes self-care practices, specifically dietary intake, physical activity, and medication-taking behaviors.

DD, self-care behaviors, and HbA_1c_ will be assessed at 3 measurement periods, at baseline (randomization), and at the third and sixth month postrandomization. DD will be assessed using the previously validated 17-item DDS [18]. HbA_1c_ will be tested at every 3-month follow-up visit as part of usual care for patients not meeting glucose targets. Self-care practices (diet, physical activity, and medication-taking behaviors) will be assessed with the respective subscales of the Summary of Diabetes Self-Care Activities questionnaire [30]. Satisfaction with HC will be assessed for the intervention arm at the end of the study (sixth month) through self-administered surveys, including Likert scale-type questions and open-ended questions. WTP for HC will be assessed through an indirect survey approach, which has been shown to be preferable because of higher internal and external validity compared with other methods [34]. In such indirect approaches, participants are confronted with different attribute combinations of various products or services (eg, HC vs alternative interventions) with assigned prices, and they choose the most preferred scenarios. Specifically, we will conduct a discrete choice experiment to assess WTP.

**Figure 2 figure2:**
[figure not shown]
Statistical power of Coaching and Education for Diabetes Distress trial to detect effect sizes from 0.4 to 1.0.

**Table 2 table2:** Measures and time frame for the Coaching and Education for Diabetes Distress trial.

Measure		Baseline	3 months from baseline	6 months from baseline
**Primary outcome measure**				
	Diabetes distress score [18]	X	X	X
**Secondary outcome measures**				
	Hemoglobin A_1c_	X	X	X
	Self-care behaviors (Medication-taking, dietary, and physical activity behaviors) using the Summary of Diabetes Self-Care Activities questionnaire [30]	X	X	X
	Willingness to pay for health coaching	X	—^a^	X
	Satisfaction with health coaching (intervention arm only)	—	—	X

^a^Not applicable.

### Data Analysis

The primary analysis will use repeated measures analysis of variance to compare mean change in DD, HbA_1c_, and self-care scores between baseline and months 3 and 6 for the 2 study arms. Satisfaction with HC will be reported as the proportion of respondents agreeing with different grades of a Likert scale. The open-ended questions on the HC satisfaction questionnaire will be analyzed qualitatively using thematic analysis. On the basis of the choices that the participants make in the discrete choice experiment, WTP for HC will be estimated by logistic regression models.

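### The primary analysis compares raw change in DDS; adjusting for the baseline DDS already collected on everyone would raise power from 80% to about 93% on the plan's own assumptions

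*Protocol article*

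**What the plan says.** The protocol article fixes three things on this point.

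- **Analysis.** The section on data analysis states: "The primary analysis will use repeated measures analysis of variance to compare mean change in DD", together with HbA1c and self-care scores, between baseline and months 3 and 6 for the two arms. No baseline covariate is named there or anywhere else in the article.
- **Sample size.** In the section on sample size determination the target is "an effect size (difference in mean change in DD between the 2 groups) of 0.5". The inputs are "a DD SD of 0.89 and 0.81, respectively, at baseline and at follow-up" and "a correlation (ρ) of 0.5 between a pair of observations made longitudinally on the same subject", with 80% power, 5% alpha, 20% attrition and 3:1 allocation, giving 39 intervention and 117 control participants.
- **Data.** In the section on measures and data collection, DDS, self-care and HbA1c are measured "at baseline (randomization), and at the third and sixth month postrandomization". The primary outcome is the 6-month change in DDS. A mean DDS of at least 2.0 is an entry criterion, so every participant will have a score at entry.

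**The concern.** When baseline is one of the occasions in a repeated measures ANOVA, the arm-by-time contrast of month 6 against baseline is the difference between arms in raw change. Raw change subtracts the whole baseline value. That is efficient only if follow-up rises one-for-one with baseline, and the plan's own figures say it does not. The excess subtraction adds noise to every participant's outcome. It also carries part of any chance baseline difference between arms into the estimate with its sign reversed. Study Arm Assignment describes random sorting to fixed arm sizes, with no stratification by DDS, so the design does nothing to limit that difference.

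Precision is the scarce resource here. The coaching arm has 39 participants, and the article says that fiscal constraints drove the 3:1 allocation. The measurement that would recover the lost precision is already being taken on everyone.

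**Working it through.** **Inputs** (all from Sample Size Determination): SD 0.89 at baseline and 0.81 at follow-up, ρ = 0.5, difference 0.5, alpha 5%, attrition 20%, 39 + 117 randomised. The article does not say whether alpha is one- or two-sided. Two-sided is assumed because it reproduces the stated power; one-sided would give 88%.

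**1. Reproduce the plan's figure.**

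- SD of change = √(0.89² + 0.81² − 2 × 0.5 × 0.89 × 0.81) = √0.7273 = 0.853.
- The smallest 1:3 completer numbers reaching 80% in a two-sample t-test are 31 + 93. Then 31/0.8 = 38.75, rounded to 39, and 93/0.8 = 116.25, rounded to 117. The total is 156, exactly as stated.
- SE = 0.853 × √(1/31 + 1/93) = 0.853 × 0.2074 = 0.177. Noncentrality = 0.5/0.177 = 2.83. Power is 80.1% (noncentral t).
- At a difference of 0.6, power is 92.0%, consistent with the article's claim of more than 90%.

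So the 80% is the power of an unadjusted comparison of change.

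**2. Slope implied by the same inputs.** 0.5 × 0.81/0.89 = 0.46, against the coefficient of 1 that raw change imposes.

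**3. Baseline-adjusted analysis, same inputs and completers.**

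- Residual SD = 0.81 × √(1 − 0.5²) = 0.701.
- Variance ratio = (0.701/0.853)² = 0.677, a 32% reduction. 1/0.677 = 1.48, equivalent to about 48% more patients.
- SE = 0.701 × 0.2074 = 0.145. Noncentrality = 3.44. Power is 92.6% (noncentral t) or 93.0% (normal).

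| At 31 vs 93 completers | Raw change | Baseline-adjusted |
|---|---|---|
| Residual SD | 0.853 | 0.701 |
| Power for 0.5 | 80.1% | 92.6% |
| Difference detectable with 80% power | 0.50 | 0.41 |
| 95% CI half-width | ±0.35 | ±0.29 |

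A simulation of 6,000 trials per scenario (31 vs 94 completers) gave 80–81% for change and 92–93% for the adjusted analysis. Type I error was about 5% for both.

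**4. Other correlations (assumed values, SDs kept).**

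| ρ | Raw change | Adjusted |
|---|---|---|
| 0.3 | 66% | 87% |
| 0.4 | 73% | 90% |
| 0.6 | 88% | 96% |
| 0.7 | 95% | 98.5% |

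**5. Chance imbalance.** The baseline difference between arms has SD 0.89 × √(1/39 + 1/117) = 0.16 DDS points. Raw change passes (1 − 0.46) = 0.54 of it into the estimate, with sign reversed: 0.54 × 0.16 = 0.09 points as randomised, or 0.54 × 0.89 × 0.2074 = 0.10 among completers. This is the whole gap between the two standard errors: 0.145² + 0.10² ≈ 0.177².

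**The case against.** **The plan is valid and consistent with itself.** Outcome, sample size and analysis all use change, N reproduces exactly, and type I error is correct. This stands. The weakness is one of efficiency, and the imbalance term in step 5 is random error already counted in the 80%, not bias.

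**Covariates may be left to an analysis plan that is not shown.** The article never uses the word unadjusted, and an analysis of change with a baseline covariate would also compare mean change. This has limited force. The article names the primary method, and its sample size rests on the unadjusted change variance. It has therefore committed to that analysis in both places.

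**The gain may be smaller than stated.** The 0.89 comes from a cited study, and requiring DDS of at least 2.0 may narrow the baseline spread. Suppose, as an assumption, that the slope stays at 0.46 and the residual SD at 0.701. A baseline SD of 0.7 then gives 85% for raw change, and 0.5 gives 89%, while the adjusted analysis stays at 92.6%. The variance saving falls from 32% to 23% and 13%. The gain also shrinks as ρ rises. This stands as a limit on size. It does not reverse the direction: under a linear model the adjusted residual variance cannot exceed the change-score variance, and the only price is one degree of freedom.

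**The stated ANOVA could be tested by its 2-df arm-by-time interaction.** Simulated power of that test is about 84% if the 0.5 effect is present at both visits, and about 72% if it is 0.25 at month 3 (assuming all correlations 0.5 and a month-3 SD of 0.81). So 80% against 93% describes only the single month-6 contrast. That is, however, the contrast on which the trial was sized, and it matches the declared 6-month outcome.

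**Conclusion.** The concern holds. On the plan's own SDs, correlation, attrition and allocation, and with a two-sided 5% test of the month-6 contrast, the unadjusted analysis has 80.1% power for a difference of 0.5 and the baseline-adjusted analysis 92.6%. The 93% is conditional on those inputs. For ρ from 0.3 to 0.7 the gain runs from 21 points down to about 3. If the entry threshold narrows the baseline SD to between 0.7 and 0.5, the gain is about 8 to 4 points. In none of these cases does adjustment lose power. The planned analysis is not invalid; it gives up precision that the trial has already paid to collect.

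**What to change.** Make the primary estimate baseline-adjusted, in one of two ways:

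- month-6 DDS regressed on arm with baseline DDS as covariate (ANCOVA); or
- a longitudinal model of the month-3 and month-6 DDS with arm, visit, arm-by-visit, baseline DDS and baseline-by-visit terms, with the month-6 arm difference as the primary contrast.

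The two need not agree exactly when month-6 data are missing, and 20% attrition is expected, so name one as primary. Use the same form for HbA1c and each self-care score, each with its own baseline. The outcome may still be described as change: with baseline in the model, analysing change or the month-6 value gives the same arm difference.

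Keep N at 156; the stated 80% then becomes conservative under the plan's inputs.

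The cost is about one sentence of analysis wording and one degree of freedom, with no extra patients, visits or measurements. The article reports recruitment continuing through December 2019, so on that timetable the change can be specified before outcomes are compared by arm.

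### Repeated-measures ANOVA as the primary analysis uses only participants scored at all three visits, although 20% attrition is expected; a mixed model would use the partial data

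*Protocol article*

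**What the plan says.** The protocol's Data Analysis section fixes one method for the primary and several secondary outcomes: "The primary analysis will use repeated measures analysis of variance". The arms are to be contrasted on change in distress, glycated haemoglobin and self-care, with scores from all three visits (baseline, month 3, month 6) in the model.

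Under Measures and Data Collection, distress "will be assessed at 3 measurement periods, at baseline (randomization), and at the third and sixth month postrandomization". The same section defines the endpoint: "The primary outcome measure will be short-term (6 months) changes in DD score".

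The Sample Size Determination section sets the numbers: "The study requires a total sample of 156 participants, 39 in the intervention arm and 117 in the control arm". The target is "an effect size (difference in mean change in DD between the 2 groups) of 0.5", with "a power of 80%, alpha (type I error rate) of 5" per cent, and the calculation is described as "accounting for a possible attrition rate of 20" per cent. It does not say whether that 20% means absence at month 6 or a gap at any visit.

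**The concern.** Classical repeated-measures ANOVA needs a score at every visit in the model. With three visits, two kinds of participant drop out of the analysis:

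- those with baseline and month 3 who leave before month 6, whose month-3 score says something about where they were heading;
- those with baseline and month 6 who missed month 3. They have the full primary outcome and are still excluded.

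The sample size compares change between two time points, but the named analysis demands three. Gaps at month 3 that come on top of loss by month 6 were not obviously budgeted for.

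A complete-case comparison of this kind is generally valid only if loss is completely at random. If leaving is related to early response, the people analysed in one arm may no longer be comparable with those in the other, and the month-3 score that could correct this is thrown away. The intervention arm has only 39 people, so each lost case there matters.

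**Working it through.** **1. Reproduce the planned sample size.** Inputs from Sample Size Determination: SD 0.89 at baseline and 0.81 at follow-up, correlation 0.5, difference 0.5, alpha 5% (two-sided reproduces the figure), power 80%, ratio 3:1, attrition 20%.

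- SD of change = √(0.89² + 0.81² − 2 × 0.5 × 0.89 × 0.81) = 0.853.
- Smaller arm: n = (1 + 1/3) × (1.960 + 0.842)² × 0.853² / 0.5² = 30.4, so 31; larger arm 3 × 31 = 93.
- Inflation: 31/0.8 = 38.75, so 39; 93/0.8 = 116.25, so 117. Total 156, as stated.

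**2. Power by share missing any visit.** Power is taken from 0.5 / [0.853 × √(1/n₁ + 1/n₂)], by the normal approximation and by the noncentral t. Shares above 20% are assumptions.

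| Complete cases (coaching + control) | Share missing any visit | Power, normal | Power, t |
|---|---|---|---|
| 31 + 93 | design target | 80.7% | 80.1% |
| 31.2 + 93.6 | 20% | 81.0% | 80.3% |
| 30 + 90 | about 23% | 79.4% | 78.8% |
| 29.2 + 87.8 | 25% | 78.4% | 77.7% |
| 28 + 84 | about 28% | 76.6% | 75.9% |
| 27.3 + 81.9 | 30% | 75.6% | 74.8% |

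The 28 + 84 row is what remains if a further 10% of the month-6 completers miss only month 3. To keep 31 + 93 complete cases, the trial would need to randomise 168 at 25% missing and 180 at 30%.

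**3. Bias if loss is informative.** These are simulations on assumed mechanisms, with SDs 0.89, 0.85 (month 3, assumed) and 0.81, and correlation 0.5 with baseline.

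*Coaching-arm loss only.* 20% leave after month 3 with log-odds of 1 to 2 per SD of the month-3 quantity. Control loss is random, the true effect is zero, and the month-3 to month-6 correlation is 0.5 to 0.7.

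| Loss depends on | Complete-case bias at month 6 |
|---|---|
| month-3 change | 0.08 to 0.16 points in favour of coaching |
| month-3 level | from 0.03 in favour of coaching to 0.01 against |

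Against the 0.5 target, 0.08/0.5 = 16% and 0.16/0.5 = 32%. A likelihood-type estimate that uses the month-3 score stays within 0.003 of zero in these scenarios.

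*By arm.* True effect 0.50, 20% loss per arm, all correlations 0.5, and log-odds 1.5 per point of month-3 change where loss is informative.

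| Arm with informative loss | Complete-case effect |
|---|---|
| coaching only | 0.60 |
| control only | 0.41 |
| both, equally | about 0.50 |

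**The case against.** Three points can fairly be made for the plan.

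First, the sample was inflated for loss. At exactly 20% missing, complete-case power is 80-81% for 0.5 and about 92% for 0.6. A reader might infer that the expected attrition by itself breaks the power; step 1 shows that it does not. The 20% may already mean any missed visit, and the protocol describes quarterly follow-up as usual care, so a high rate of isolated month-3 gaps is not self-evident. This stands in full. What remains is the lack of margin.

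Second, a reader might infer that the method inflates the coaching effect. The protocol gives no ground for a direction. The upward figure needs non-responders to leave the coaching arm selectively, with loss driven by change rather than level. Eight sessions in one arm make that conceivable, but all sessions are by telephone precisely to limit inconvenience and cost. This also stands: upward bias is one scenario among several.

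Third, the article nowhere says that incomplete participants are excluded, the label is sometimes used loosely for a mixed model, and handling of missing data may be set out in documents not shown. The absence of such detail is indeed no finding. But the article does name a specific primary method, and taken at its ordinary meaning that method is the complete-case one. If a mixed model is intended, one sentence settles it.

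**Conclusion.** The point holds as a recommendation to change the named method. Classical repeated-measures ANOVA on three visits wastes partial data, excludes some people whose primary outcome is complete, and rests on loss being completely at random.

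On power, the consequence is a thin margin rather than a shortfall. The design sits at 80-81% with the planned loss, and at about 78% or 75% if 25% or 30% miss any visit. Those rates are assumptions.

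On bias, the size and sign depend on which arm loses which patients. The scenarios run from 0.16 points in favour of coaching, through roughly none, to about 0.09 points against it (0.50 − 0.41). None of these mechanisms is stated in the protocol, so they show what the method leaves exposed, not what will happen.

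All of this assumes that the term is meant in its classical sense.

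**What to change.** In Data Analysis, replace repeated-measures ANOVA with a likelihood-based linear mixed model for repeated measures: arm, visit, arm-by-visit interaction and unstructured within-person covariance. Fit it to all randomised participants in their assigned arms, using every available distress score. Name the month-6 arm contrast as the primary estimate, to match the stated endpoint. Adjustment for baseline distress is an optional further gain.

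The cost is a change of analysis wording and slightly more analysis work; no added visits, data or participants are needed. The model relies on data being missing at random given the observed scores. That is weaker than completely at random but still an assumption, and the model does not protect against loss that depends on unobserved scores.
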